## Introduction

Restrictive practices are measures that limit a person’s [1] rights or freedom of movement [2]. In acute mental health services, a shared goal exists among people receiving care, carers, professionals, policymakers, advocates, and organisations to eliminate these restrictive practices and promote therapeutic relationships [3]. This goal has been recently strengthened, with calls for rights-based mental health systems, person-centred care, stigma reduction, greater inclusion, and an end to coercion [4]. However, the evidence on interventions supporting this goal remains limited in quality and considerations of culturally safe, co-produced, strengths-based, and complexity-informed approaches [5]. Beyond a few well-known programmes, most initiatives in adult inpatient settings also exist only in grey literature and are not well-described [6], with study designs and protocols not openly available.

Seclusion, physical restraint, and forced medication are restrictive practices that exemplify legal coercion [7]. These regulated and documented interventions are employed when less stringent measures have been exhausted in response to a perceived risk of harm [8]. There are differences in the language, meaning, regulation, monitoring, and prevalence of these practices in adult mental health inpatient services worldwide, including Australia [9]. Attitudes toward restrictive practices also vary, with many healthcare professionals, especially nurses, seeing them as unavoidable, as a last resort [10], as something that could not be fully eradicated from practice [11], and as apt within staffing constraints and limited available options [12]. Restrcitive practices are considered traumatic and are associated with a range of harms, including but not limited to isolation for Indigenous people [13] and disruption of therapeutic relationships between individuals receiving care and nurses [14].

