### The Safe Steps for De-escalation

In a regional adult mental health inpatient unit in New South Wales (NSW), Australia, a lack of structure to therapeutic responding was evident in the absence of a consistent content and approach to de-escalation training, the varying skill levels of nurses in managing distress and conflict, and the persistently high rates of physical restraint and seclusion [31]. In response, a new model was introduced in the unit in 2019 to monitor restrictive practices and up-skill nurses, and implement the 2017 NSW review recommendations on seclusion, restraint, and observation [32]. The model was implemented alongside strength-based review meetings, where nurses received feedback on how well they practice relational competencies. The reviews conducted between January 2019 and March 2020 were linked to a reduction in the use of seclusion (incidence rate ratios [IRR] = 0.37, 95% CI [0.24, 0.57], p < .001), compared to an equivalent timeframe before their implementation [33]. Measures of experienced support by the people receiving care in the unit also increased by 14% in 2019–2020, exceeding the 80% national benchmark [34].

This model is called the *Safe Steps for De-escalation*—or simply the *Safe Steps.* It is a clinician initiative centred on a four-step, user-friendly framework for therapeutic responding that begins with helping the person receiving care to identify the issue or problem, through to establishing expected behaviours. There is evidence for the structure and progression of therapeutic responses in the Safe Steps [35] that offers nurses a platform to exercise their authentic voice and intuitive competencies in supporting work towards making acute units safe. The Safe Steps targets nurses’ relational competencies to increase focus on the self-management of people receiving care and therapeutic relationships. Its implementation is supported by value-based training and regular data-informed restrictive practice review meetings.

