#### Mental health nursing de-escalation logs.

The mental health nursing de-escalation log developed by a clinician (MF) in collaboration with another clinician (AT) has five sections: i) incident details, ii) aggression type, iii) interventions, iv) situational aggression levels, and v) outcomes, covering 51 variables. It records contextual information (date, location, number of staff involved), direction of aggression (e.g., individual to nurse), and lists interventions like the four Safe Steps and other non-relational, non-coercive de-escalation techniques. Situational aggression levels are rated on a 6-point scale from calm to physical aggression with weapons. Outcomes include restrictive practice use (e.g., seclusion, physical restraint, sedation via intramuscular injections), Code Black, time out, care level allocation, physical injuries, and incident management system reporting. Nurses will be trained to complete these logs, which they will contemporaneously cross-reference with unit data to minimise recall bias. Concurrent validation of the restrictive practice use outcomes will be attempted.

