### Analysis plan

Quantitative and qualitative analyses will be used to answer the evaluation’s objectives. Consultations with statisticians occurred for the range of statistical treatments employed in this evaluation. Various packages in R [74] and RStudio [60] will be maximised for the quantitative analyses, and Matplotlib [75] will be utilised for visualising outcomes. Each hypothesis will be supported if outcomes are statistically significant at p < .05.

Poisson mixed-effects models [56] will be used for count data and linear regression models for continuous outcomes, to determine whether these outcomes differ according to intervention implementation and time points. Data cleaning and validation, assumption checks, model diagnostics, and follow-up analyses will be undertaken. Negative binomial mixed models, zero-inflated models, and linear mixed-effect models may be used depending on the model’s diagnostics. Covariates in the mixed-effect models will include the acute care unit, calendar month, day, year, and the day within the study period for each daily event aggregate. Model selection will prioritise parsimony and explanatory strength. Inverse probability weighting (IPW) will be applied in the between- and within-group comparisons. Using the ipw package [76], IPW will be used to balance covariates, including but not limited to the average harm scores of daily aggregates, the number of high observation beds, the number of seclusion rooms, and other confounds (i.e., physical restraint and Code Blacks are closely interrelated, influencing each other’s occurrence or implementation [77]). Listed covariates for balancing will be used, subject to the data’s fit and the statistical model’s ability to achieve convergence in the IPW approach.

Hierarchical clustering analysis [78] will support the emergence of co-occurring mental health nursing response clusters, which will then be the fixed effect in modelling differential associations with restrictive practices, physical injuries, and situational aggression. This cluster and regression analysis constitutes the between-cluster comparison to identify the most active response clusters contributing most to Safe Steps’ overall impact.

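### Which response cluster a log falls in can depend on how the incident ended, so the cluster ranking cannot show which responses drive Safe Steps' impact

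*Protocol article*

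**What the plan says.** The Design section lists three comparisons. The third, between clusters, is meant to find which co-occurring responses contribute to the overall impact. The Analysis plan builds the clusters by hierarchical clustering and makes cluster the fixed effect in models for restrictive practices, physical injuries and situational aggression. It then states the reading: "This cluster and regression analysis constitutes the between-cluster comparison to identify the most active response clusters contributing most to" Safe Steps' overall impact. The Discussion repeats that reading as a strength of the evaluation.

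The section on the Safe Steps describes an ordered framework that "begins with helping the person receiving care to identify the issue or problem, through to establishing expected behaviours", and adds: "There is evidence for the structure and progression of therapeutic responses in the Safe Steps".

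The section on the de-escalation logs says that the log "lists interventions like the four Safe Steps and other non-relational, non-coercive de-escalation techniques". The same form holds the outcomes: "Outcomes include restrictive practice use (e.g., seclusion, physical restraint, sedation via intramuscular injections), Code Black, time out" and others. On context, the article says: "It records contextual information (date, location, number of staff involved), direction of aggression (e.g., individual to nurse"). No order or time of steps relative to the outcome is described.

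Inverse probability weighting is assigned to the between- and within-group comparisons; the between-cluster comparison is not named.

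**The concern.** The explanatory variable is the set of responses recorded by the end of the incident, and the way the incident ended is the outcome. With ordered steps, a restrictive practice that begins after the first or second step may leave the later ones undone. A person who settles early may not need them. In either case, having all four steps on the log partly describes how the incident went, and a model with cluster on the right-hand side can find a difference where the steps do nothing.

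The named safeguards do not reach this. Weighting is described for the other two comparisons. Situational aggression is modelled as an outcome, not used to adjust, and the article does not say at what point in the incident it is rated. The fidelity checklist, according to Table 1, assesses programme components and not individual steps.

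At stake is the statement about active responses. The between-group test of effectiveness is unaffected.

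**Working it through.** The article gives no figure for this comparison, so there is nothing to reproduce. The check asks what the cluster comparison would show if the steps had no effect. Every rate below is an assumption; the article gives none.

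**Model.** After step k (k = 1, 2, 3) the incident ends in a restrictive practice with probability r_k, ends in calm with probability c_k, or goes on to the next step. After step 4 it ends in a restrictive practice with probability f and otherwise in calm. The steps change nothing. The restricted share among logs with exactly k steps is r_k / (r_k + c_k) for k = 1 to 3, and f for k = 4.

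| Scenario | r_1, r_2, r_3 | c_1, c_2, c_3 | f | Restricted share at 1 / 2 / 3 / 4 steps |
|---|---|---|---|---|
| A: only restriction cuts short | .08, .08, .08 | 0, 0, 0 | .08 | 1.00 / 1.00 / 1.00 / .08 |
| B: only calm cuts short | 0, 0, 0 | .20, .20, .20 | .20 | 0 / 0 / 0 / .20 |
| C: both, constant 1:3 ratio | .08, .08, .08 | .24, .24, .24 | .25 | .25 / .25 / .25 / .25 |
| D: restriction likelier early | .12, .08, .04 | .10, .20, .30 | .10 | .55 / .29 / .12 / .10 |
| E: calm likelier early | .04, .08, .12 | .30, .20, .10 | .40 | .12 / .29 / .55 / .40 |

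Examples: D at one step is .12/(.12 + .10) = .55; E at one step is .04/(.04 + .30) = .12; C at every early step is .08/(.08 + .24) = .25.

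In A and D the full sequence looks best, in B it looks worst, in E a single step looks best, and in C there is no difference. D and E contain no difference in severity between incidents. Their gradients over one to three steps do not depend on the choice of f.

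**Severity.** Taking C and letting severity vary between incidents (standard deviation 1 on the logit scale, raising restriction and lowering settling) gave simulated shares of .285 / .319 / .345 / .385.

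**With clustering.** Simulated null data: 600 logs per run, 100 runs, four step indicators plus three irrelevant techniques, Ward clustering into four clusters, chi-square test of restriction by cluster at .05. A cluster effect was declared in:

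- A: 100% of runs
- C with varying severity: 30%
- C: 7%
- steps recorded independently of the outcome: 3–4%

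With 100 runs, the Monte Carlo standard error at a true 5% is √(.05 × .95/100) = .022, so 7% is compatible with 5%.

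**The case against.** The main objection is that truncation is inferred. No section says that a restrictive practice or early calm stops the steps, or that unreached steps are left blank. The Introduction points the other way for restriction: "These regulated and documented interventions are employed when less stringent measures have been exhausted in response to a perceived risk of harm". That stands as a limit on the claim. It does not rescue the comparison, because if restriction follows only after all the steps, early calm can still shorten the sequence, which is scenario B.

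A reader might infer that the ranking is certainly biased, and by a large factor in favour of the full sequence. The document does not support this. Take 8% restriction and 5–30% settling per step. Shorter logs then show .08/(.08 + .05) = .62 to .08/(.08 + .30) = .21 restricted, against .08 in four-step logs: ratios of .13 to .38. But this counts the 62–87% of four-step incidents that are neither settled nor restricted (1 − .08 − .30 to 1 − .08 − .05) as not restricted. If they run on at the same rates, their share is also r/(r + c) and the ratio is 1.0.

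The calculation is also not the planned model. The Sample section speaks of daily aggregates, and the article does not say whether the cluster model works per log or per day. Pooling incidents by day may dilute the dependence, so the per-log figures do not transfer.

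Adjusting for severity at onset would help where severity is the only source, as the contrast between C and its varying-severity version suggests. It would not remove the bias in D or E.

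Finally, the Abstract lists clusters among other outcomes, the Analysis plan itself speaks of associations, and the Discussion treats change mechanisms as uncertain. That lowers the severity. The contribution reading nevertheless stands in the Design, Analysis plan and Discussion sections.

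**Conclusion.** The point holds in a limited form. The article fixes the explanatory variable, the model and the interpretation, and the interpretation does not follow from the other two. Ordered steps, one log for steps and outcomes, and no described timing mean that cluster membership can depend on the ending. If the ending does cut the sequence short, the ranking would generally be biased even with inactive steps. The bias vanishes in special cases, such as a constant ratio of the two endings with equal severity, but the article gives no reason to expect that case. Neither sign nor size can be derived from the document; the scenarios show only that the sign depends on unknown rates. Severity is minor to moderate: the Design section ties the two sets of hypotheses to the between- and within-group comparisons, and none to this one.

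**What to change.** In the Design, Analysis plan and Discussion sections, report the cluster results as descriptive associations and remove the statements that they identify the most active responses or those contributing most to the overall impact.

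Where the logs allow steps to be ordered relative to the start of a restrictive practice, add a landmark contrast: among incidents still open after step k, going on to step k+1 versus not, adjusted for aggression level at onset if it was recorded then. Where order cannot be established, stay with description.

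Two alternatives should not be adopted. Making Step 1 started versus not started the primary contrast has the same flaw, because an incident restricted at once never reaches Step 1. Changing the log comes too late: the Recruitment and consent section says that the study had reached its third time point at first submission and that collection ends on 15 April 2025.

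The cost is a change of wording and, where the data permit, one added analysis of logged data. The downside is a weaker claim about active components.

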### Recruitment and consent

The current evaluation will employ various recruitment strategies, with consent procedures tailored to each data collection activity. The implementation of Safe Steps follows an opt-in model, with recruitment proceeding through an asynchronous, multi-centre approach [65]. Each site independently decides when to implement Safe Steps, allowing for autonomy and flexibility, while ensuring consistency in the intended intervention across settings. Recruitment began at the first intervention site on 1st March 2024, with the latest site starting on 16th April 2024. Baseline data collection for the unit register, ims+, and eMeds data, covering the year before each site’s recruitment start date, commenced alongside recruitment. The final recruitment and data collection will conclude one year after the latest recruitment start, on 15th April 2025. At the time of the initial submission of the protocol for publication consideration, the study has reached its third time point.

For event-based analyses, the consent to access administrative data from unit registers and incident management systems was waived, because individual and nurse participant identifiers will not be gathered, nor will the data be re-identifiable. On the other hand, completion of the de-escalation log will serve as implied consent, and no identifying nurse details will be recorded. Identifying individual information will be gathered solely to help complete the logs, after which it will be removed and replaced with a randomly assigned study code before being shared with the first author.

For survey-based measures, peer worker-led surveys will be open to individuals over 18 who can consent to participate in the research. The only exclusion criteria are individuals receiving care with an identified need for an interpreter who refuse to use interpretation services adjacent to the unit. Increasing access to research participation with interpretation services was done with the consideration of guidance from the state-wide service that streamlines care pathways for culturally and linguistically diverse (CALD) individuals.

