Given the quality checks associated with national key performance indicators for mental health services, there is no expected missing data for the primary outcomes. However, log data may undergo multiple imputations under different missing data mechanisms [79] to minimise bias due to missing data. A day without log data will contribute to the missingness rate. Lastly, fidelity scores will be described statistically and plotted in a graph.

For survey-based measures, a one-way analysis of variance will be used to assess differences over time in people measures. In contrast, a paired t-test will examine changes in nurses’ measures over time. Missing data of not more than 20% will be imputed using multiple imputations [80]. Measures with less than 80% of the total items completed will be excluded. Non-parametric statistical models may be used if distributional assumptions are violated.

For the qualitative strand, pluses and wishes, transcribed interview responses, and focus group discussion data, will be analysed using NVivo 12 Pro software [81] and alternatively through a spreadsheet. An analytical process [82,83] that involves re-reading transcriptions for familiarisation, organising data, coding and condensed coding, and refining thematic results through a team approach, will be systematically led by the first author to integrate multiple perspectives. A codebook will be maintained [84]. Individual participants can review their responses for accuracy before analysis [85].

Machine learning techniques, including but not limited to random forest [86] and Boruta algorithm [87], will be maximised to undertake a feature analysis on the most important drivers of aggression and restrictive practice use. Qualitative log responses on triggers of de-escalation will be coded and considered in feature analyses.

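### Counting every day without a de-escalation log as missing mixes days with nothing to log with days on which an episode went unlogged, so the reported log missingness rate will be wrong

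*Protocol article*

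**What the plan says.** The Analysis plan first states that, because of quality checks on national indicators, "there is no expected missing data for the primary outcomes". It treats the log differently: "log data may undergo multiple imputations under different missing data mechanisms". The next sentence gives the rule at issue: "A day without log data will contribute to the missingness rate". No exception is made for days on which no episode occurred.

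The Measures section describes the log as having five sections, "i) incident details, ii) aggression type, iii) interventions, iv) situational aggression levels, and v) outcomes, covering 51 variables". On aggression it says: "Situational aggression levels are rated on a 6-point scale from calm to physical aggression with weapons". It adds that nurses complete logs, "which they will contemporaneously cross-reference with unit data to minimise recall bias". Under Recruitment and consent, "completion of the de-escalation log will serve as implied consent", so completing a log is voluntary.

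**The concern.** Every section of the log describes something that happened: an incident, the type of aggression, the response, the level reached and the outcome. The lowest rating, calm, is a level given to a situation someone chose to log; it is not described as a daily entry for an uneventful day. A unit-day with no episode therefore leaves no log when everyone does the job correctly.

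The rule puts that day in the same class as a day on which an episode occurred and nobody completed the form. The first is a true absence of events; the second is missing data. Two things follow:

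- The missingness rate, which readers will use to judge the quality of the log data, becomes partly a measure of how quiet the units were.
- If the rate also decides what is imputed, a quiet day would be given an aggression level, a nursing response and an outcome. No such values exist to be recovered, whatever missing-data mechanism is assumed.

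The analyses that draw on the log are the between-cluster comparison of nursing responses (one of the three planned comparisons in the Design section), the situational aggression outcome, and the feature analysis of triggers.

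**Working it through.** The article states no log missingness rate and no episode rate, so there is no figure to reproduce. The calculation shows what the rule does under stated assumptions.

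**Inputs from the article**

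- Three intervention units (Setting) and a one-year intervention (Intervention): 3 × 365 = 1,095 unit-days.
- A day without a log counts as missing (Analysis plan).

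**Assumptions**

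- Episodes per unit-day are Poisson with mean *m*, from 0.1 to 3.
- Every episode is logged, so true missingness is 0%.
- For the imputation columns only: every log-free day is imputed, with logged days as the only donors.

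**Formulas**

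- Share of days called missing = P(no episode) = exp(−*m*).
- Mean on logged days = *m* / (1 − exp(−*m*)). After imputation every day has this mean.
- Inflation of the daily mean = 1 / (1 − exp(−*m*)).

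Example, *m* = 0.5: exp(−0.5) = 0.607, so 61% of days are called missing. The mean after imputation is 0.5 / 0.393 = 1.27, and the inflation is 1 / 0.393 = 2.54.

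The episode totals are averages of 500 simulated years of 1,095 unit-days.

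| *m* per unit-day | Days called missing (truth 0%) | Inflation if all are imputed | True episodes | Episodes added |
|---|---|---|---|---|
| 0.1 | 90% | 10.5 | 109 | 1,043 |
| 0.25 | 78% | 4.5 | 274 | 964 |
| 0.5 | 61% | 2.5 | 547 | 844 |
| 1 | 37% | 1.6 | 1,096 | 637 |
| 2 | 14% | 1.16 | 2,192 | 340 |
| 3 | 5% | 1.05 | 3,284 | 171 |

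The second column follows from the written rule alone. The third and fifth need the imputation assumption as well.

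**With incomplete logging**, the daily rule still does not measure missing logs. Suppose *m* = 3 and each episode is logged independently with probability one half. Logged episodes then have mean 1.5, and log-free days are exp(−1.5) = 22%, although 50% of logs are missing. A day with one of its three episodes logged counts as complete. The rule can therefore err in either direction, depending on how busy the unit is.

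**The case against.** **Imputation is optional.** The plan says log data may be imputed and names more than one mechanism. The sentence on log-free days concerns a rate; it does not say that whole days will be filled in. A reader might infer that the plan will create fictitious episodes, but the article does not support that: imputation would have to be used, applied to whole days, and drawn from logged days. This stands. Only the wrong missingness rate follows from the text as written.

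**The units may be busy.** The three intervention units have 75 beds, 25 on average, and the log covers de-escalation generally, including situations rated calm. Several episodes a day is a plausible assumption, and the effect is then small. If a day means a calendar day pooled over the three units, the mean triples: at 1 per unit-day, log-free days fall from 37% to exp(−3) = 5%. This also stands, and is why the whole range is shown. Quoting only the large multiples would be one-sided.

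**The main results are untouched.** A reader might fear for the seclusion, restraint, sedation and injury comparisons. Those use administrative records, and the second set of hypotheses uses surveys; neither rests on the log.

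**Some log-free days really are missing.** Logging is voluntary, so the rule is partly right. But it has no means of separating those days from quiet ones. The cross-reference to unit data is described for logs that are being completed; it does not classify days without one.

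**Missingness need not rise if the intervention works.** Fewer incidents would mean fewer logs, but the logs feed the intervention's own review meetings, so good uptake could increase logging. The direction is not established.

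**Conclusion.** The point holds as a fault in a stated rule, not as detail left to another document. Applied as written to an incident-triggered form with no nil return, the rule counts days with nothing to log as missing, and the reported rate does not measure missing logs. With complete logging and Poisson means of 0.1 to 3 episodes per unit-day, it would report 90% down to 5% missing where the truth is 0%. If whole log-free days were then imputed from logged days, the daily mean would be inflated about 10-fold down to 1.05-fold. Where the trial falls in that range is unknown, because the article gives no episode rate.

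The damage is confined to the between-cluster comparison, situational aggression and the feature analysis. Severity: should-fix.

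**What to change.** Replace the daily rule with one defined per episode:

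1. Count a log as missing when the unit register, ims+ or eMeds shows an event on that unit and date and there is no log.
2. Report log-free days with no recorded event separately, under a label such as *no recorded episode*. Neither count them as missing nor impute them, and do not call them true zeros.
3. Limit imputation to missing items within completed logs, or to episodes known from other records to have occurred.
4. Run the cluster–outcome analysis on actual logged episodes.
5. State the limitation: the log is meant to capture successful de-escalation, which may leave no trace in administrative systems. Such episodes cannot be detected if unlogged, so the missing-log rate is a lower bound that reflects recorded events only.

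The cost is a few sentences in the Analysis plan and a linkage by unit and date. The log already records date and location, and the three administrative sources are already being collected, so no new data are needed.
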